## Abstract

**Background:**

In armed conflict, injuries commonly affect the extremities and contamination with foreign material often increases the risk of infection. The use of negative-pressure wound therapy has been described in the treatment of acute conflict-related wounds, but reports are retrospective and with limited follow-up.

**Objective:**

The objective of this study is to investigate the effectiveness and safety of negative-pressure wound therapy use in the treatment of patients with conflict-related extremity wounds.

**Methods:**

This is a multisite, superiority, pragmatic randomized controlled trial. We are considering for inclusion patients 18 years of age and older who are presenting with a conflict-related extremity wound within 72 hours after injury. Patients are block randomly assigned to either negative-pressure wound therapy or standard treatment in a 1:1 ratio. The primary end point is wound closure by day 5. Secondary end points include length of stay, wound infection, sepsis, wound complications, death, and health-related quality of life. We will explore economic outcomes, including direct health care costs and cost effectiveness, in a substudy. Data are collected at baseline and at each dressing change, and participants are followed for up to 3 months. We will base the primary statistical analysis on intention-to-treat.

**Results:**

The trial is ongoing. Patient enrollment started in June 2015. We expect to publish findings from the trial by the end of 2019.

**Conclusions:**

To the best of our knowledge, there has been no randomized trial of negative-pressure wound therapy in this context. We expect that our findings will increase the knowledge to establish best-treatment strategies.

**Trial Registration:**

ClinicalTrials.gov NCT02444598; http://clinicaltrials.gov/ct2/show/NCT02444598 (Archived by WebCite at http://www.webcitation.org/72hjI2XNX)

**International Registered Report Identifier (IRRID):**

DERR1-10.2196/12334

## Introduction

### Background

During armed conflict, injuries commonly affect the extremities, among both civilians [1] and combatants [2]. These injuries are often contaminated with foreign material, increasing the risk of infection [3,4]. Traditionally, conflict-related wounds are surgically treated with debridement of devitalized or contaminated tissue and then covered with a nonadhesive dressing. After 3 to 5 days, the wound is generally examined a second time in the operating room [5].

Negative-pressure wound therapy (NPWT) is widely used in the treatment of wounds and is claimed to promote wound healing and prevent infectious complications. The technique involves covering the wound with a solid foam followed by a plastic film through which a negative pressure is applied. Any wound and tissue fluid is drawn away from the area and collected into a canister. NPWT is suggested by expert consensus for use in a range of surgical applications, including after or in between debridements, as a bridge to definite closure of soft tissue wounds [6]. The technique has previously been used in the treatment of acute conflict-related wounds, but existing reports are retrospective and with limited follow-up [7-10]. Two independent Cochrane reviews of NPWT for the treatment of surgical wounds [11] and traumatic wounds [12] were inconclusive due to the lack of suitably powered, high-quality trials.

### Summary of Potential Risks and Benefits

Both treatment methods (NPWT and conventional dressings) are well established and used in the treatment of acute and chronic wounds. As it is unknown whether there is any difference in outcome between the two treatment modalities, neither patient group may be regarded as receiving preferential treatment. In this study, we will allocate treatment at the end of the first surgery so there is no difference between the groups in terms of surgical risks.

NPWT has not regularly been used at the study sites prior to this study. The introduction of NPWT is not associated with any serious risks compared with standard treatment. Potential benefits of NPWT are shortened healing time and fewer infectious complications. The occlusive dressing may, on the other hand, cause more infections or delay the identification of infection. Other potential risks include pain, mainly associated with dressing changes [13], and bleeding, predominantly minor bleeding from granulation tissue [14]. Conventional wound dressing has the potential benefit of being a safe treatment method used for many years. Since this method permits air into the wound, the risk of health care–associated infections is potentially higher.

### Objective

The objective of this study is to evaluate the effectiveness and safety of NPWT in the treatment of traumatic extremity wounds in a context associated with a high level of contamination and infection.

## Methods

### Study Design

This is a multisite, superiority, pragmatic randomized controlled trial comparing NPWT versus conventional dressing methods in the treatment of patients with conflict-related extremity wounds (ClinicalTrials.gov NCT02444598).

### End Points

The primary end point is wound closure by day 5, by suture, flap, or split-thickness skin graft.

The coprimary end point is net clinical benefit, defined as a composite of wound closure by day 5 and freedom from any bleeding, infection, sepsis, or loss of index limb.

The secondary end points are (1) rate of wound healing, defined as days to wound closure by suture, flap, or split-thickness skin graft; (2) wound infection, defined as purulent discharge [15]; (3) wound size ratio at day 14 (wound size day 14 compared with size day 0, ie, wound healing rate after 14 days); (4) time until wound is deemed no longer requiring professional care; (5) number of surgeries; (6) time to hospital discharge; (7) quality-of-life aspects; (8) wound healing at follow-up days 14 and 30, and at 3 months; (9) bleeding leading to blood transfusion; (10) sepsis; (11) limb amputation (limb with wound included in the study); (12) death; (13) direct health care costs (substudy); and (14) cost effectiveness (substudy).

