### Sample Size and Power Calculation

The sample size calculation was based on detection of a difference of 25% between treatment groups in the proportion of patients for the primary outcome. We estimated the expected rate of patients reaching the primary outcome at day 5 to be 75% in the NPWT group and 50% in the control group. Based on a power of 80% and a significance level of 5%, we calculated that we would need a minimum sample size of 116 patients (58 per group) to detect a significant difference in the proportions. To adjust for dropouts, we aim to include 200 patients (100 per group).

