### Statistical Analysis

We will perform analyses on an intention-to-treat basis with a 2-sided significance level of .05. The primary end point (wound closure by day 5) will be presented as proportions with a 95% confidence interval for the difference in proportions. We will analyze the coprimary end point with standard survival analysis using proportional hazards for comparison of the treatment arms. For the primary end point, we will also perform a per-protocol analysis, excluding patients who did not receive the planned treatment or did not survive to day 5. We will report baseline characteristics as means and standard deviations or numbers and percentages, as appropriate. Subgroup analyses will include age, injury mechanism, initial injury severity, associated fracture versus no fracture, and initial wound size.

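### The coprimary net clinical benefit composite does not count death as a failure, and its bleeding component has no threshold, unlike secondary end point 9

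*Protocol article*

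**What the plan says.** Under End Points, the protocol article names closure by day 5 as the primary end point and adds a coprimary called net clinical benefit, which is "defined as a composite of wound closure by day 5 and freedom from any bleeding, infection, sepsis, or loss of index limb". A numbered list of secondary end points comes next and contains wound infection (item 2, defined by purulent discharge), "bleeding leading to blood transfusion" (item 9), sepsis (item 10), amputation of the study limb (item 11) and death (item 12). The first four correspond to the four harms in the composite. Death has no counterpart there.

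The Summary of Potential Risks and Benefits lists, among the possible risks of NPWT, "bleeding, predominantly minor bleeding from granulation tissue".

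Statistical Analysis states: "We will analyze the coprimary end point with standard survival analysis using proportional hazards for comparison of the treatment arms". It does not mention death for this end point. Its one rule on death concerns the per-protocol analysis of the primary end point, "excluding patients who did not receive the planned treatment or did not survive to day 5". The composite has no stated window for its harm components, while the abstract says that "participants are followed for up to 3 months".

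**The concern.** A net clinical benefit measure is meant to set the gain (early closure) against the harms. This one has a problem at each end of the harm scale.

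- **Most serious harm.** Death is absent, so a patient can satisfy every condition of the composite and be dead.
- **Mildest harm.** Bleeding carries no severity threshold. A closed patient with slight bleeding fails in the same way as one with sepsis or a lost limb. The same section applies a transfusion threshold when bleeding is an end point in its own right, so two bleeding definitions stand side by side. The protocol itself expects bleeding under NPWT to be mostly minor. If such bleeding is recorded and is more frequent under NPWT, it could offset a real closure advantage.

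The end point is coprimary, so its definition bears on how the trial's main result will be read.

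**Working it through.** **1. Death.** Apply the definition to four kinds of patient:

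| Patient | Closure by day 5 | Listed harm | Scored as net benefit |
|---|---|---|---|
| Dies before closure | no | – | no |
| Closed, then dies with recorded sepsis, infection or bleeding | yes | yes | no |
| Closed, then dies with no listed event | yes | no | **yes** |
| Closed, alive, no listed event | yes | no | yes |

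Only the third row is wrong. It stays wrong whether the window ends at day 5 or at 3 months, because death after closure is not a failure in either. The window only changes how many patients fall in that row.

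The article gives no death rate. As an assumption, let a fraction d of closed patients die with no listed event. Per 100 randomized, the number miscounted is 100 × closure rate × d:

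- d = 1%: 0.75 (NPWT), 0.5 (control)
- d = 2%: 1.5, 1.0
- d = 5%: 3.75, 2.5

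With d = 5% under NPWT and 0% in control, and no other events, the reported difference is 75 − 50 = 25 points. With death counted it is 71.25 − 50 = 21.25 points.

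**2. The plan's own sample size.** Sample Size and Power Calculation assumes closure in "75% in the NPWT group and 50% in the control group", with 80% power and a 5% level. With pooled variance, two-sided, and mean proportion 0.625:

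n = [1.96·√(2·0.625·0.375) + 0.842·√(0.75·0.25 + 0.5·0.5)]² / 0.25² = 57.7, so 58 per group, 116 in total.

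This reproduces the stated figure. For closure alone, power is about 96% at 100 per arm. The calculation covers closure only and makes no allowance for harms in the composite.

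**3. Effect of the harm components.** Net benefit rate = closure rate × (1 − c), where c is the proportion of closed patients with any listed harm. For control, c = 11% is an assumption, set to the wound infection rate quoted under Setting as a stand-in. The NPWT value is varied. Power is the exact binomial power of the pooled two-sided z-test at 5%, with 100 per arm.

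| c NPWT | c control | Net benefit NPWT | Net benefit control | Difference (points) | Power |
|---|---|---|---|---|---|
| 11% | 11% | 66.75% | 44.5% | 22.25 | 90% |
| 15% | 11% | 63.75% | 44.5% | 19.25 | 80% |
| 20% | 11% | 60.0% | 44.5% | 15.5 | 61% |
| 30% | 11% | 52.5% | 44.5% | 8.0 | 22% |
| 30% | 30% | 52.5% | 35.0% | 17.5 | 72% |

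The normal-approximation formula gives values one to two points lower. The loss depends mainly on how far the two arms differ in recorded harms, and less on how common harms are overall.

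**The case against.** **Shorthand.** The four harms in the composite match secondary items 9, 2, 10 and 11. The composite may simply refer to those events in brief, with the word any governing the whole list. Infection is also left undefined there, and a reader would naturally take its definition from item 2. This is a fair reading, and it means the bleeding point is a conflict of wording rather than proof of intent. It still has to be settled, because the text equally allows the literal reading. It does not help with death, which is in the list of end points but not in the composite.

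**Full protocol.** Component definitions often sit in the full protocol or analysis plan. That is true of operational detail, including how deaths enter the proportional hazards model, and no fault is claimed there. But the article gives the composite's membership outright, and that is what omits death.

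**Recording of minor bleeding.** A reader might infer that unblinded staff will turn trivial oozing into failures, mainly under NPWT. The documents do not show this. Table 1 lists wound and treatment details without a bleeding item, and no bleeding rate is given for either arm. If freshly debrided wounds bleed in both arms, the relevant row is 30% v 30%, with power of about 72%.

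**Hidden mortality.** A reader might also infer that the composite could conceal a mortality signal. It could not conceal it from the trial: death is secondary end point 12 and is reported separately. Equal numbers of such deaths in the two arms would change the treatment difference little.

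**Test used.** The power figures come from a test of two proportions, not from the planned proportional hazards analysis, and 100 per arm includes the allowance for dropouts. Both objections stand, so the figures are illustrations only.

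**Conclusion.** The point holds on the wording. The composite omits death, so a patient who dies after closure with no listed event counts as a net benefit, and nothing elsewhere in the article corrects this. Its bleeding component conflicts with item 9 and, taken literally, weights minor bleeding like sepsis or limb loss.

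The size is uncertain. The death gap is confined to one kind of patient and may be small. The power range of about 90% down to 22% rests on assumed complication rates. The 22% figure needs a 19-point excess under NPWT (30% v 11%), which the documents neither state nor imply, so it should not be quoted as the expected power.

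The primary end point and its sample size are unaffected. This should be fixed, but it does not threaten the trial's main analysis.

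**What to change.** By a documented amendment, made before anyone compares outcomes by arm, define net clinical benefit as closure by day 5 and, over one stated time window for all components, alive and free of:

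- bleeding that leads to transfusion (as in item 9),
- wound infection shown by purulent discharge (item 2),
- sepsis (item 10),
- loss of the index limb (item 11).

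Report whatever minor bleeding has been recorded as safety data, and analyze the composite as now published as a sensitivity analysis, so that the effect of the change is visible.

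The components of the revised composite are all listed end points already, so the change adds no end point to those planned. The cost is that a coprimary end point is amended during an open-label trial that has enrolled since June 2015. The date, the reason and the fact that no data had been examined by arm should therefore be recorded. Minor bleeding also moves out of the composite into a separate table.

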### Participants

Patients 18 years of age and older presenting at the hospital within 72 hours of sustaining a conflict-related extremity wound are included as they present at the emergency department. In case of multiple wounds, we are selecting the extremity wound with the estimated largest area. Patients are included if they are transferred from another hospital within 72 hours of initial trauma. Patients who present with wounds considered ready for primary closure by suture, flap, or split-thickness skin graft are excluded. Local or systemic infections are treated according to local standard protocols. Wounds in need of debridement are debrided according to International Committee of the Red Cross war surgery protocols [5].

### Setting

Jordan is an upper-middle-income country [16], currently hosting 655,000 Syrian refugees [17]. Médecins Sans Frontières/Doctors Without Borders (MSF), an international nongovernmental organization, runs an emergency trauma project at the Jordan Ministry of Health hospital in Ar Ramtha, 5 km from the Syrian border. Patients within the project receive treatment for blast and gunshot wounds sustained in the Syrian armed conflict. Discharged patients are sometimes continuously treated by MSF in Zaatari refugee camp. The wound infection rate among patients receiving acute surgical treatment at the project has been found to be 11%, with 3 out of 4 patients infected by multidrug-resistant bacteria [18]. Physicians within the project have found wound management to be a major challenge [19]. Patient enrollment in Ar Ramtha, Jordan started in June 2015.

Iraq is an upper-middle-income country [16]. Emergency Hospital is a trauma center in Erbil, Iraqi Kurdistan that is run by a local nongovernmental organization called Emergency Management Center. Most patients receive treatment for conflict-related injuries, and the hospital was one of the key medical institutions receiving the injured from Mosul during the Iraqi offensive against the so-called Islamic State of Iraq and Syria during October 2016 to July 2017 [20]. Patient enrollment in Erbil is ongoing since May 2017.

### Randomization and Blinding

We use a computer-generated randomization code with random variation of 2 fixed block sizes to achieve balance in the allocation of participants to the 2 treatment arms and reduce the opportunity for bias and confounding. Each site has its own dedicated randomization list respecting the 1:1 ratio. The sealed randomization envelopes are opened by the operating room nurse at the end of the first surgery, but before the wound dressing is applied. By randomizing after the operation, we eliminate the risk of treatment allocation influencing the surgeon’s choice of debridement technique. Wound photographs will be evaluated by 2 independent trained evaluators who are blinded to the treatment allocation. Due to the nature of the treatment methods, blinding of the patients or staff involved in the treatment would not be possible.

### Interventions

Patients in the NPWT group receive treatment using a Conformité Européenne–marked professional device with continuous negative pressure of 125 mm Hg. Patients in the control group are treated with conventional wound therapy according to International Committee of the Red Cross war surgery protocols: a nonadhesive dressing covered with a bandage [5]. The exact details of the dressing technique are left to the discretion of the treating surgeon. Dressing details are recorded. All patients receive prophylactic narrow-spectrum antibiotic agents. Fractures are generally immobilized with external fixation. Dressing change frequencies are determined by the treating physician, generally every 3 to 5 days. Any further wound dressing will follow the allocated treatment. Wounds are treated until wound closure. Estimated median duration of treatment (control group) is 5 days.

### Follow-Up Procedures

Follow up is done at each dressing change, at hospital discharge, at days 14 and 30 and at 3 months following the day of randomization (Table 1). Full wound healing or size of wound at the treatment location is noted. Discharged patients either return to the hospital for follow-up or are contacted by phone. If possible, wounds are photo documented and evaluated as described below.

### Quality of Life

We use the 20-item Self Reporting Questionnaire (SRQ-20) to screen for psychological distress [21]. In addition, wound-specific quality-of-life details are recorded, including noise generated by the NPWT pump, movement impairment, skin irritation, odor, sleep quality, discomfort during dressing changes, and pain. SRQ-20 scores and wound-specific quality-of-life details are recorded at baseline and before hospital discharge.

### Sample Size and Power Calculation

The sample size calculation was based on detection of a difference of 25% between treatment groups in the proportion of patients for the primary outcome. We estimated the expected rate of patients reaching the primary outcome at day 5 to be 75% in the NPWT group and 50% in the control group. Based on a power of 80% and a significance level of 5%, we calculated that we would need a minimum sample size of 116 patients (58 per group) to detect a significant difference in the proportions. To adjust for dropouts, we aim to include 200 patients (100 per group).

### Data Collection

Dedicated research nurses collect and enter data into paper-based case report forms during the study period. For all enrolled patients, contact details including mobile phone number are collected. Wounds are photo documented at day 0, at every dressing change, at day 14, and, if possible, at 1 and 3 months’ follow-up. Photo documentation is done in a standardized way with a single-colored background and an adhesive paper ruler attached to the edge of the wound.

**Table 1 table1:** Timeline of trial activities.

Time point	Activity
Baseline	Patient inclusion (consent within 5 days of randomization), patient details, injury details, wound details, photograph of wound, SRQ-20^a^ scores, and quality-of-life details
End of first surgery	Randomization, allocation of treatment, wound details, treatment details, photograph of wound
Dressing change	Treatment details, wound details, photograph of wound
Hospital discharge	Treatment details, wound details, SRQ-20 scores, and quality-of-life details
Day 14	Treatment details, wound details, photograph of wound
Day 30	Treatment details, wound details, photograph of wound
3 months	Treatment details, wound details, photograph of wound

^a^SRQ-20: 20-item Self Reporting Questionnaire.

### Data Management

We will use the EpiData entry software, version 4.4.3.1 (The EpiData Association) to build a database. All data will remain anonymous throughout the data entry and analysis process. Only the research team will know the participants’ names. Identification codes will be safeguarded at the research facilities for the duration of the study.

### Statistical Analysis

We will perform analyses on an intention-to-treat basis with a 2-sided significance level of .05. The primary end point (wound closure by day 5) will be presented as proportions with a 95% confidence interval for the difference in proportions. We will analyze the coprimary end point with standard survival analysis using proportional hazards for comparison of the treatment arms. For the primary end point, we will also perform a per-protocol analysis, excluding patients who did not receive the planned treatment or did not survive to day 5. We will report baseline characteristics as means and standard deviations or numbers and percentages, as appropriate. Subgroup analyses will include age, injury mechanism, initial injury severity, associated fracture versus no fracture, and initial wound size.

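### Closure by day 5 and the coprimary net clinical benefit fall under one 2-sided .05 level with no testing order, while sample size and abstract recognise closure only

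*Protocol article*

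**What the plan says.** In the protocol article:

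- **End Points.** Closure by day 5 is the primary end point. A second end point is then given similar rank: "The coprimary end point is net clinical benefit". It requires closure by day 5 and, in addition, no bleeding, infection, sepsis or loss of the index limb.
- **Statistical Analysis.** One level covers everything: "We will perform analyses on an intention-to-treat basis with a 2-sided significance level of .05". Closure is reported as a difference in proportions with a 95% confidence interval. The coprimary is compared between arms by proportional hazards. Only closure also gets a per-protocol analysis.
- **Sample Size and Power Calculation.** The calculation is "based on detection of a difference of 25% between treatment groups in the proportion of patients for the primary outcome", with assumed rates of "75% in the NPWT group and 50% in the control group". It gives 58 per group at 80% power and a 5% level. No rate, effect or power is given for the coprimary. The increase to 100 per group is attributed to dropouts.
- **Abstract, Methods.** "The primary end point is wound closure by day 5". The coprimary is not mentioned, either as a primary or among the secondary end points.

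**The concern.** Coprimary is used in two opposite senses: success on either end point is enough, or success on both is required. The article does not say which it means, and it gives no testing order that would settle the matter. The abstract and the End Points section also disagree on how many end points carry the trial's conclusion.

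The two senses have different costs. Under either-suffices, two tests at .05 give an overall false-positive rate above 5%. Under both-required, the error rate is safe, but the power for a positive trial is the joint power, for which the article gives no figure. At stake is what counts as a positive trial. That should be fixed before results are seen, particularly because patients and treating staff are not blinded.

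**Working it through.** **Inputs from the article.** Closure 75% versus 50%; 2-sided 5%; 80% power; 58 per group as the minimum and 100 per group as the target (Sample Size and Power Calculation). The only complication rate given is an 11% wound infection rate at the Jordanian project (Setting).

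**Assumptions, not in the article.** The composite is treated as a yes/no outcome, equal to closure with no component failure. A share *f* of closed wounds fails a component: 11% (borrowed from the infection rate), 30% or 40%, equal in both arms, plus one case with 5% on NPWT and 11% on control.

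**1. The plan's own figure.** Pooled two-proportion formula, no continuity correction, with p̄ = 0.625:

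n = [1.960·√(2·0.625·0.375) + 0.842·√(0.75·0.25 + 0.50·0.50)]² / 0.25² = (1.342 + 0.557)² / 0.0625 = 57.7, so 58 per group.

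This reproduces the plan. Power is 80.2% at 58 per group and 96.0% at 100.

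**2. If either end point suffices.** For two independent tests the overall error would be 1 − 0.95² = 9.75%. The composite is nested in closure, so the tests are positively correlated and the true figure is lower. With closure p = 0.50 in both arms and composite rate p₂ = p(1 − *f*), the correlation is p₂(1 − p) / √[p(1 − p)·p₂(1 − p₂)]: about 0.90 at *f* = 11% and 0.65 at *f* = 40%. Simulating 400,000 trials at 58 per group, with no difference on either end point:

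| *f* | Error if either suffices |
|---|---|
| 11% | 7.1% |
| 40% | 8.7% |

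More patients do not remove this excess.

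**3. If both must succeed.** Joint power can never exceed the power for closure, so at 58 per group about 80% is the ceiling. With *f* = 11% in both arms, the composite rates are 0.75·0.89 = 66.75% and 0.50·0.89 = 44.5%, a difference of 22.25 points. With p̄ = 0.556, the same formula gives

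n = (1.377 + 0.576)² / 0.2225² = 77.1, so 78 per group for the composite alone.

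With failure of 5% on NPWT and 11% on control, the rates are 0.75·0.95 = 71.25% and 44.5%, a difference of 26.75 points. Simulated joint power:

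| Component failure, NPWT / control | 58 per group | 100 evaluable per group |
|---|---|---|
| 11% / 11% | 66% | 89% |
| 30% / 30% | 46% | 71% |
| 5% / 11% | 77% | 95% |

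At 80 evaluable per group with 11% in both arms, joint power is about 80%.

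**4. If closure alone carries the claim.** There is one test at .05, with 80.2% power at 58 per group. Both stated figures hold.

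**The case against.** A reader might infer that, whichever rule applies, either the 5% or the 80% must be wrong. The article does not support that. Step 4 meets both figures, and testing closure first and the composite only afterwards would also keep both with no change in numbers. Nor is the 80% a misstatement: the Sample Size section ties it expressly to the primary outcome.

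The article also gives closure a leading place: it is the end point named in the abstract, the basis of the sample size and the only one with a per-protocol analysis. A testing order may stand in an analysis plan that is not shown. This weakens the point but does not remove it. A lead role is not a testing order, the label coprimary suggests equal standing, and the abstract and End Points section differ within the article itself.

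One might also infer that the composite must show a smaller difference than closure. That holds only if complications are equal in the two arms. The Summary of Potential Risks and Benefits allows that NPWT could lower or raise infections, and the 5% versus 11% case yields a larger difference than 25 points. The ceiling on joint power stands; the size of the shortfall is not fixed by the article.

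Two further limits stand. The calculations use a binary test, whereas the plan uses proportional hazards. The 11% is one project's infection rate among its acute surgical patients, not a failure rate among wounds closed by day 5. Finally, at the full target of 100 evaluable per group, joint power passes 80% under the 11% assumption, although the article reserves those extra patients for dropouts.

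**Conclusion.** The point holds in a limited form. As written, the text allows two unordered claims at .05, with the trial sized for one of them. The consequence depends on the rule that is missing:

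- **Closure alone:** no fault in the 5% or the 80%.
- **Either suffices:** overall error of about 7% to 9% at 58 per group, for assumed component failure of 11% to 40%; 9.75% is only the independence limit.
- **Both required:** error no more than about 5%, but power at 58 per group at most about 80%, and about 66% under equal 11% failure. Whether 100 per group is enough depends on how many patients are evaluable and on the failure rate.

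The need for a stated rule does not depend on the assumed failure rates; the sizes do. This should be fixed, but it does not invalidate the sample size for closure.

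**What to change.** 1. In End Points, make closure by day 5 the sole primary end point and relabel net clinical benefit as a key secondary end point.
2. In Statistical Analysis, state the order: closure first at 2-sided .05; net clinical benefit at .05 only if closure is significant, otherwise descriptive.
3. In Sample Size and Power Calculation, state that the 80% power applies to closure only.
4. Bring the abstract into line, so that all four places give the same hierarchy.

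This keeps the error for the two claims together at 5% and leaves the power for closure unchanged. It needs no more patients and no new data. The cost is wording, and one claim given up: net clinical benefit cannot be declared on its own if closure fails.
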